#### Direct Adherence

Adherence is measured by frequency of app use (number of times participants log in per day), duration of use (number of hours per day), and consistency of data recording (interactions with the app, like using the diary, changes in the questionnaire answers, and entering hypoglycemia data).

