My day: a diary is available to record various items [Figure 1H]. Participants are able to easily and intuitively record their fruit and vegetable intake, alcohol and tobacco consumption, and sunscreen use every day. They are able to customize the diary to choose the items they want to record. They see a graphical presentation of the records of the last 7 days, with a marker for their personal goal [Figure 1I], as well as individual and personalized messages generated with the use of AI for the improvement of their goals. People with T1D can also record their hypoglycemic events.Assess your lifestyle: participants complete questionnaires that provide data for WARIFA to personalize their risk estimation and recommendations. These questionnaires include basic variables (age, gender, weight, and height), lifestyle habits (alcohol consumption, smoking, and physical activity), eating habits, and sun exposure, as well as additional risk factors for melanoma. Once the questionnaires have been completed, the app delivers the first messages with personalized recommendations. If the user enters this section at another stage in the trial and changes data in the questionnaires, new recommendations are generated and delivered to the user.My top recommendations: personalized recommendations appear for each participant each day, based on the data obtained through the initial questionnaires and how far they are from the recommended target for each item (Figure 1A). These recommendations are based on scientific evidence and updated World Health Organization guidelines.My health predictions: will give access to risk calculators (Figure 1B) for different NCDs (T2D, CVD, COPD, and melanoma) with personalized risk estimation over the next 10 years. During the WARIFA project, some risk calculators were developed, including the cardiovascular risk calculator for T1D [29]. The melanoma risk calculator was developed based on the first primary risk prediction tool created by the Melanoma Institute Australia [31]. The FINDRISK calculator, which has been validated in several European countries, is used to calculate the risk of T2D [32]. To calculate cardiovascular risk in the general population, the SCORE2/SCORE2OP calculator was used; this has been validated in the European countries participating in the study [33,34]. Finally, the self-scored COPD population screener questionnaire [35] was used to screen for COPD in smokers, since there is no COPD risk calculator validated in the European population. In all cases, the personalized risk of the different NCDs is accompanied by an explanatory message. If the COPD-Q score is high, it is recommended that participants visit their health service physician for further assessment.My community: through the use of geolocation (if permission is granted), it provides personalized recommendations based on the UV and air quality indices in the participant’s geographical area (Figures 1C,1D,1E,1F, and 1G). A link to a web page [36] with additional health-relevant information (air pollution and UV rays, statistics on NCDs of the population, lifestyle habits...) about the area where the user is located is also displayed.Step functionality: shows the number of steps taken by participants at any point in each day, as well as a graphical presentation of the number of steps for the last 7 days (Figure 1J). Recording is automatic via the physical activity monitor.Heart rate function: shows the current heart rate and a graph with its evolution in relation to the measurements in the last 24 hours. The source of the data is the physical activity monitor.Sleep function: shows today’s hours of sleep and a bar graph of the hours of sleep the last 7 days recorded by the physical activity monitor.Diabetes functionality: people with T1D can view their glucose data in near real time (with a delay of 30 minutes) by connecting to the glucose sensor (Figure 2). They can also view historical glucose data through various graphs, such as time in different ranges (Figures 2B and 2C), glucose management index, and hypoglycemic events. Using AI, they receive an estimate of the interstitial glucose prediction over the coming 30 minutes and 2 hours (Figure 2D), as well as a personalized risk of nocturnal hypoglycemia (Figure 2A).Settings and other functions: in this section, participants can customize which parts of the WARIFA app they want to see, as well as the notifications, sounds, fonts, and language used.

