### Control Group

The control group received a low-intensity intervention, with access to a WARIFA app version where almost all the functionalities mentioned above are available, except for the diary, risk calculators, and personalized recommendations. AI features such as near real-time glucose prediction, night time hypoglycemia risk, and motivational feedback in the top recommendations section are not available in this version, either. Data are collected in a similar manner, and an activity monitor is provided for the duration of the study, too.

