### Outcomes

#### Overview

The primary outcome is a participant-defined goal, whose fulfillment is assessed at the end of the study using a Likert scale ranging from 1 (“far below expectations”) to 10 (“far above expectations”) [38].

Participants can choose their own goal from a range of options: increase fruit and vegetable consumption, increase physical activity, reduce alcohol consumption, stop smoking, improve sun protection behavior, and reduce the number of weekly hypoglycemic episodes (the latter only for T1D participants).

The secondary outcomes are: frequency of app use, time spent using the app, consistency in data recording, changes in eating habits, increase in physical activity, reduction in smoking and alcohol consumption, changes in sun protection behavior, total cholesterol, high-density lipoprotein (HDL) cholesterol, low-density lipoprotein cholesterol, non-HDL cholesterol, triglycerides, weight, BMI, body fat, lean mass, abdominal, waist and biceps circumference, abdominal skinfold thickness, tricipital skinfold thickness, dynamometry, sit to stand 5 repetitions test, perceived quality of life, acquired knowledge, self-efficacy, and usability.

For participants with T1D, hypoglycemic events (number of episodes of at least 15-minute duration with a glucose concentration of <70 mg/dL according to the CGM and manually registered episodes), HbA_1c_, average glucose (average glucose in mg/dL over the last 14 days), glucose management indicator (a measure of glycemic control calculated from average glucose, which is an estimation of HbA_1c_) and time in target range (% of time in the last 14 days that glucose is within (70-180mg/dL), below (<70 mg/dL), above (181-240 mg/dL), or significantly above (>240 mg/dL) the recommended target will be measured.

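### Consistency of data recording counts diary use, but the control app has no diary, so this one engagement measure is biased toward the intervention

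*Protocol article*

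**What the plan says.** The Overview under Outcomes includes this measure in its list of secondary outcomes: "frequency of app use, time spent using the app, consistency in data recording, changes in eating habits". Nothing there limits it to one arm or to functions that both arms share.

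Direct Adherence names three measures: log-ins per day, hours of use per day, and "consistency of data recording (interactions with the app, like using the diary, changes in the questionnaire answers, and entering hypoglycemia data".

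The Intervention section describes the diary as the tool for daily manual logging ("My day: a diary is available to record various items"). In the same item it adds: "People with T1D can also record their hypoglycemic events". The questionnaires belong to a different function, Assess your lifestyle, where re-entry is foreseen: "If the user enters this section at another stage in the trial and changes data in the questionnaires".

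The Control Group section describes an app in which "almost all the functionalities mentioned above are available, except for the diary, risk calculators, and personalized recommendations". It also says of the control arm: "Data are collected in a similar manner".

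**The concern.** An engagement measure can be compared between randomized arms only if both arms have the same opportunity to score on it. Here one named contributor, diary use, cannot occur in the control arm. The diary is also the tool for everyday logging of diet, alcohol, tobacco and sunscreen, so it could plausibly supply many of the counted interactions.

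What is at stake is interpretation. The Background argues that personalization can raise engagement and adherence. A higher recording count in the intervention arm could be presented as support for that argument when it shows only that a logging feature was switched on in one version and off in the other.

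**Working it through.** The article states no figure for this measure, so there is nothing to reproduce. The check sets the definition against the features of each version and then illustrates the consequence.

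**Step 1. Features by arm**

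| Named interaction | Intervention app | Control app | Basis |
|---|---|---|---|
| Diary use | Yes | No | Express exclusion in Control Group |
| Questionnaire changes | Yes | Apparently yes | Assess your lifestyle is not among the exclusions |
| Hypoglycemia entry (T1D only) | Yes | Unclear | Intervention describes it only within the diary; Outcomes Overview and Biomedical Outcomes mention manual registration without separating arms |

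One of the three is certainly unavailable to controls, one appears shared, and one is unresolved. The unresolved one concerns only participants with T1D, who were recruited only in Spain (Power and Sample Size), where 34 people enrolled in total (Results).

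**Step 2. Expected difference when engagement is equal**

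Give each participant an engagement level drawn from the same distribution in both arms, with mean 1. Let *q* be the mean number of shared interactions per person and *d* the mean number of diary entries, possible in the intervention arm only.

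- Intervention mean = *q* + *d*
- Control mean = *q*
- Difference = (*q* + *d*) − *q* = *d*

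The whole difference is the diary count. Its direction does not depend on the values chosen.

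**Step 3. How often this would look significant**

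Inputs from the Results section: 42 intervention and 46 control participants. Assumptions, because the documents give no rates: gamma-mixed Poisson counts (gamma shape 1, scale 1), no true difference in engagement, a two-sided Mann-Whitney test at 0.05, and 1,000 simulated trials per cell.

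| Mean diary entries *d* | p<0.05 with *q* = 2 | p<0.05 with *q* = 5 |
|---|---|---|
| 0 (shared interactions only) | 5.0% | 4.1% |
| 1 | 29.0% | 10.6% |
| 2 | 65.5% | 24.1% |
| 5 | 99.2% | 74.4% |
| 10 | 100% | 98.3% |

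The simulated mean differences followed *d*, for example 5.03 for *d* = 5 with *q* = 2. The first row shows the effect of the repair: with the diary left out, the false-positive rate is about nominal.

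**The case against.** The strongest reply is that the list of interactions opens with a word that makes it illustrative. No composite, weights or derivation are given, and the Statistical Analysis section specifies no test for this variable. A condensed article may leave those details to an analysis plan that is not shown, and that plan might describe the measure within arm only. This stands as far as the derivation goes. It does not remove the point, because the article itself names diary use in the definition of a secondary outcome and itself withholds the diary from controls. Adding other interactions would dilute the bias but not remove it while diary use is counted. The general statement that control data are "Data are collected in a similar manner" names no substitute for the diary.

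Four stronger readings are tempting, and the documents do not support them.

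- **A reader might infer that two of the three components are zero for all 46 controls.** Only the diary is expressly removed. The absence of hypoglycemia entry is inferred from where one sentence sits. For participants without T1D that component does not apply in either arm, so their zeros do not come from the app version.
- **A reader might infer that questionnaire editing is tilted too**, because in the intervention app, when a user "changes data in the questionnaires, new recommendations are generated and delivered to the user". The questionnaires appear open to both arms. If recommendations lead people to edit more, that is an effect of personalization, which the trial sets out to measure.
- **A reader might infer that a significant result is guaranteed.** The illustration runs from about 11% to 100% across its diary scenarios. The direction is built in; significance is not.
- **A reader might infer that the whole engagement comparison is invalid.** Log-ins per day and hours per day can be measured in both arms. Recording consistency is one of three engagement measures and stands third in the list of secondary outcomes.

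**Conclusion.** The point holds for one secondary outcome. As defined, recording consistency includes an activity that controls cannot perform, so a between-arm comparison favors the intervention through feature availability. The direction follows from the article's own text. It rests on two conditions: that the measure is compared between arms, as its place among the trial's secondary outcomes suggests, and that diary use is counted as the definition says.

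The size is not known. It depends on how much of the count comes from the diary, and the simulated percentages rest on assumed rates. Whether T1D controls face a second missing component is an open question for the sponsor to answer. Log-in frequency and duration are not zero by design in controls, and the primary outcome and its analysis are untouched.

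**What to change.** - Restrict the between-arm comparison of recording consistency to interactions available in both versions, such as questionnaire changes. Report it beside the log-ins per day and hours per day that are already planned.
- Report diary entries as adherence within the intervention arm only, with no between-arm test.
- State whether control participants with T1D could enter hypoglycemia manually. If they could not, treat those entries in the same way as the diary.

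The article says the data are still being analyzed and that the analysts are blinded, so the definition can be corrected and recorded before allocation is revealed. The change redefines a derived variable and needs no new data collection. It should not rely on other usage measures, such as device synchronization days or screen openings, unless the sponsor confirms they were logged, because the article does not describe them. The cost is small: the between-arm measure has fewer components.

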#### Behavior Change

Changes in dietary habits, tobacco and alcohol consumption, and sunscreen use are measured by diary entries. Changes in physical activity (steps) are automatically measured by the physical activity monitor.

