### Statistical Analysis

Descriptive results will be presented as mean (SDs), or median (IQRs) for continuous variables, and frequencies and percentages for categorical variables. The primary endpoint is the difference in Likert score between the 2 groups in the self-reported achievement of the individual, self-defined aim at the end of the study. The intervention and control groups will be compared using a Student *t* test (2-tailed) or a Mann-Whitney *U* test. We will also perform linear regression to compare the groups with adjustment for the stratification factor center. For comparison of changes in variables measured at baseline and end of study, we will use linear regression or logistic regression adjusting for the baseline measurement [48]. Logarithmic transformation may be used. A *P* value below .05 will be considered significant.

An intention-to-treat analysis will be performed (including all randomized participants, regardless of their adherence to the intervention).

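### The diary named as the source for diet, tobacco, alcohol and sunscreen outcomes is absent from the control app, so that measure gives no between-arm effect

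*Protocol article*

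**What the plan says.** All references are to the protocol article.

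- **Status of the outcomes.** The Overview under Outcomes lists among the secondary outcomes "changes in eating habits, increase in physical activity, reduction in smoking and alcohol consumption, changes in sun protection behavior".
- **Measurement.** Behavior Change gives the source: "Changes in dietary habits, tobacco and alcohol consumption, and sunscreen use are measured by diary entries". It names no second source for these four. Physical activity is measured separately, as steps from the activity monitor.
- **What the diary is.** The Intervention section describes a diary within the app: "Participants are able to easily and intuitively record their fruit and vegetable intake, alcohol and tobacco consumption, and sunscreen use every day". Recording is optional by item: "They are able to customize the diary to choose the items they want to record".
- **Control app.** In the control version "almost all the functionalities mentioned above are available, except for the diary, risk calculators, and personalized recommendations". The same section adds: "Data are collected in a similar manner".
- **Analysis.** For variables measured at baseline and end of study, Statistical Analysis says "we will use linear regression or logistic regression adjusting for the baseline measurement".
- **Adherence.** Direct Adherence includes "consistency of data recording (interactions with the app, like using the diary, changes in the questionnaire answers, and entering hypoglycemia data".

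**The concern.** The article names a specific instrument for four behaviour outcomes and separately says that one arm does not have it. The aim is to compare the personalised app with the nonpersonalised one, and the hypothesis names diet, physical activity, alcohol, smoking and sun protection as the behaviours expected to improve. If the diary stays the source, the results for four of these five become uncontrolled changes over time in intervention users who chose what to record. They could not be attributed to personalisation.

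A related issue affects the adherence measure. Using the diary counts towards consistency of data recording, and only one arm can do it.

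**Working it through.** The article gives no figure to reproduce on this point. The check is a comparison of sections plus simple counts.

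**1. Is it the same diary?** Yes. The diary in the Intervention section records fruit and vegetables, alcohol, tobacco and sunscreen, the same four domains that Behavior Change assigns to diary entries. The Control Group section removes the diary from the functions described in that Intervention section. The Abstract agrees: it ties food logging to the intervention app and does not list a diary among the features common to both versions.

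**2. How many participants can supply the named measure?** The Results section gives 42 intervention and 46 control participants, 88 in total.

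- Intervention: at most 42, i.e. 42/88 = 48%, and fewer for any item that users chose not to record.
- Control: 0 of 46. The share with no diary is 46/88 = 52%.

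**3. How many outcomes are affected?** Objective and Hypothesis names five general behaviours: eating, physical activity, alcohol, smoking and sun protection. Four of the five are assigned to the diary. Physical activity is not.

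**4. Can the planned model be fitted?** The regression compares groups on an end value adjusted for a baseline value. With diary data in one arm only, the group term cannot be estimated. The diary also gives no pre-randomisation baseline: according to Randomization and Blinding, the feature set opens only once the participant has been randomised.

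**5. Is there another source in both arms?** Possibly.

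- The Intervention section describes in-app questionnaires covering alcohol, smoking, eating habits and sun exposure. They are not among the functions removed from the control app.
- The same section says questionnaires were completed in the app at all centers, and Table 1 schedules questionnaires at the initial and final visits. Unlike the blood tests and examinations, that row is not limited to Spain. This matters because Norway and Romania, with 34 + 20 = 54 of the 88 participants, had no in-person visits.
- Against this, the lifestyle questionnaires are presented as input for personalising risk and advice, not as an outcome measure. Returning to them later is described as something a user may do. Table 1 does not say which questionnaires its row covers. An end-of-study repeat is therefore plausible but not established.

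**6. Consistency of data recording.** Three example interactions are given: diary use, changed questionnaire answers and hypoglycemia entries. Diary use is impossible in the control app. The other two are not explicitly removed, although hypoglycemia recording is described for participants with T1D as part of the diary function. No scoring rule is given, and no specific between-arm test is named for this outcome.

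**The case against.** The strongest reply is that the controls are not without data. The in-app questionnaires cover the same behaviours, were not removed from the control version, and are scheduled at both ends of the study in Table 1. The statement that data collection is similar can be read as referring to those shared questionnaires and sensors. This is also a condensed article, so the full protocol may name the control-arm source. Finally, these are secondary outcomes in a long list, and the Discussion already concedes that the sample may be too small for many of them.

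Much of this stands. A reader might infer that controls have no information at all on diet, smoking, alcohol and sun protection, that these behaviours cannot be compared by any means, and that steps are the only behaviour with data in both arms. The documents do not support that. They show only that controls have no diary data. Nor do they show that the recording-consistency outcome favours the intervention by construction. That would follow only if the arms are compared on a count that includes diary use.

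The reply does not remove the conflict. Leaving detail to a fuller document would be an omission. Here the article states a source that does not exist in one arm. The sentence on similar collection names no replacement for the diary, and Behavior Change does not mention the questionnaires. The caveat about sample size concerns power and does not disclose this problem.

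**Conclusion.** The point holds for the diary-based measure. As defined, change in diet, tobacco, alcohol and sunscreen use can be observed in at most 42 of 88 participants, all in the intervention arm. No between-arm effect can be estimated from it for four of the five general behaviours in the hypothesis. This rests on reading the removal of the diary from the control app literally, which the rest of the article supports.

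Whether these behaviours can be compared by questionnaire depends on something the article does not settle: whether the lifestyle, eating and sun-exposure items were answered again at the end of study in both arms. The concern about recording consistency is conditional on a between-arm comparison that counts diary use. The primary comparison and the steps outcome do not use the diary as their measure and are not threatened.

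**What to change.** Reconcile Control Group, Direct Adherence and Behavior Change, and settle the following before any unblinded comparison:

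1. Name the in-app lifestyle, eating and sun-exposure questionnaires as the source for these four outcomes, for those items answered at baseline and end of study in both arms.
2. Compare arms on the end-of-study answer, adjusted for the baseline answer and the randomisation strata (T1D status and center).
3. Declare this as a change of outcome source made after data collection. Follow-up ended in June 2025, so it cannot be presented as the planned measure.
4. Report diary data descriptively, for the intervention arm only, noting that users chose which items to record.
5. For any item not repeated at the end, state that no between-arm result exists.
6. If consistency of data recording is compared between arms, count only interactions possible in both app versions.

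No new data collection is needed. The work is in wording, analysis and reporting. There are two real costs: questionnaire answers are coarser and rely more on recall than daily records, and the change of source is post hoc, so these results carry less weight than a comparison planned on that measure from the outset.
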